### Baseline characteristics

After recruitment and initial screening, details covering demographic data, lifestyle, medications, identification of other diseases, anthropometric assessments, and cardiovascular variables—i.e., blood pressure and heart rate (HR)—will be collected.

### Randomization and allocation

Randomization will be performed after baseline assessments. Sequentially numbered opaque sealed envelopes will be prepared ahead of time and randomly assigned by a computer-generated table of random numbers in a 1:1 proportion. A person blinded to the study protocol will perform the randomization and provide the group assignment to the treating physical therapist. Volunteers will be allocated to the water group, which will be submitted to the 12-week DWR-IT program, or to the control group, which will not be submitted to intervention and will be instructed not to engage in any kind of structured physical exercise training and to keep the life activities identified at baseline. The International Physical Activity Questionnaire (IPAQ) will be applied before and after the intervention in order to assess the level of physical activity. Failure to follow the recommendations is an exclusion criterion in the study (Fig. 2).

**Fig. 2 Fig2:**
[figure not shown]
Flow diagram of the randomized clinical trial. Diagram of the randomized clinical trial. Detailed information about volunteer recruitment and selection and follow-up during the 12 weeks. *Abbreviations*: *6MWT* six-minute walk test, *BMI* body mass index, *CG* control group, *ESS* Epworth Sleepiness Scale, *FFQ* food frequency questionnaire, *PSQI* Pittsburgh Sleep Quality Index, *IWQOL-LITE* questionnaire on the Impact of Weight on Quality of Life-lite, *WG* water group

### Procedures

#### Anthropometry measures and body composition

Body mass (in kilograms) will be measured by using a digital anthropometric scale (Filizola^®^, Coats Corrente, São Paulo, SP, Brazil). A stadiometer (0.5 cm accuracy) will be used to measure the participant’s height (in meters). BMI will be calculated by using body weight measurements and height by the equation: BMI = kg/m^2^ [20].

An inextensible cellulose anthropometric tape will be used to measure the abdominal circumference [21]. Body composition will be evaluated by using Biodynamics TBW^®^ equipment (model 310, version 8.01; Biodynamics Corp., Shoreline, WA, USA) [22].

#### Six-minute walk test

This test evaluates the maximum distance travelled in six min while walking on the demarcated distance measures. There will be two tests with a 30-min interval between them in order to rule out learning and anxiety variables. The test with the greater distance achieved will be picked for analysis [23, 24].

#### Short form of impact of weight on quality of life

This consists of 31 items divided into five domains: physical function, self-esteem, sexual life, distress in public places, and work. The total score of each domain varies from 0 to 100; “0” corresponds to the worst general health condition and “100” corresponds to the best overall health status [25].

#### Muscle strength and endurance test

The chair stand test (CST) evaluates inner limb muscle strength and endurance and consists of 30-s sit-to-stand repetition movements in a chair without using the upper limbs [24]. The arm curl test (ACT) evaluates upper limb strength and endurance and consists of performing the greatest number of elbow flexion and extension for 30 s with 2-kg dumbbells for women and 4-kg dumbbells for men [26]. After both tests are performed, the number of repetitions will be recorded.

#### Sleep quality

The Pittsburgh Sleep Quality Index (PSQI), composed of 19 items, will be applied. The maximum score of this instrument is 21 points; scores above 5 are indicative of poor sleep quality [26]. The Epworth Sleepiness Scale (ESS) evaluates the likelihood of falling asleep while performing daily activities. Results between 0 and 10 points indicate absence of drowsiness; between 10 and 16 points, mild drowsiness; between 16 and 20 points, moderate drowsiness; and between 20 and 24 points, severe somnolence [27].

#### Food frequency questionnaire

This instrument is composed of a list of foods, distributed into 14 food groups, taking into account the frequency and quantity of each food consumed [28].

#### Intervention and follow-up periods

The intervention program will comprise 36 sessions, three times a week (in alternate days) during the morning, for 12 weeks, performed in a heated pool (32 °C). Sessions will be held in groups of no more than four volunteers and will be supervised by at least two therapists.

#### Water group (intervention group)

For the DWR-IT program, volunteers will use a Deep Runner vest (Floty^®^, Indaiatuba, SP, Brazil) and cardiac frequency meter (Polar^®^, Electro, Oi, Finland) for HR control and monitoring. To calculate the intensity of DWR-IT, the heart rate maxima (HRmax) will be recorded in the terrestrial environment by using the following equation: HRmax = 220 – age [29]. Next, the volunteers will remain immersed in the orthostatic position with water at the level of the sternum. After 5 min of rest, the HR will be measured. Afterwards, the immersion bradycardia (ΔHR), which in turn depends on the depth, temperature, and posture during the exercise, will be calculated [29]. The following formula HRmax - ΔHR will be applied to calculate the heart rate of volunteers in the aquatic environment, the following HRmax - ΔHR equation will be used [30]. During each DWR-IT session, the subjective perception of effort will be monitored and recorded [31].
First week: adaptation to a liquid environment and DWR-IT learning (44 min).Second and third week: warm-up of 2 min, then the exercise with an intensity of 60% to 65% of HRmax in the water, lasting 34 min. Two moments of sprints with 10 s for 30 s of rest (four series) were performed between the continuous exercises. After the training, 2 min of cool down was performed.Fourth to sixth week: the same procedures were performed as described in item b, but the continuous exercises lasted 33 min and five sprints were performed.Seventh to ninth week: the same procedures described in item b were performed, but the continuous exercises had an intensity of 66% to 70% of HRmax in the water, lasting 31 min. Three moments of sprints (four series) were performed among the continuous exercises.Tenth to twelfth week: the same procedures were performed as described in item b, but the continuous exercises had an intensity of 66% to 70% of the HRmax in the water, lasting 30 min, and three sprints (five series). Figure 3 shows the schematic diagram of the DWR-IT program.

**Fig. 3 Fig3:**
[figure not shown]
Description of aquatic therapy program. Detailed information about the intervention protocol, with the sprints and intensities determined for each intervention week

#### Control group

The control group will not undergo any form of treatment. Volunteers will be instructed not to change their daily usual activities or diet or participate in other physical activities. During intervention, the volunteers will be monitored by phone calls from the researchers every week, and IPAQ and food frequency questionnaire (FFQ) will be used to monitor and control the level of physical activity and the frequency and quantity of food consumed; both will be applied before intervention, at week 6, and after the intervention period. If there are changes in dietary habits or level of physical activity, the volunteers will be excluded from the study.

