Aquatic exercise is highly recommended because of its numerous benefits to the human body through the use of the water’s buoyancy, which can help decrease body fat while maintaining superior stability compared with ground exercises [15]. The deep water running in interval training (DWR-IT) is a new approach in the field of aquatic exercise to control obesity and aims to increase energy expenditure, improve cardiovascular fitness, and reduce body fat percentage [16].

DWR-IT is an aquatic aerobic exercise performed in relatively deep pools and consists of simulated running while wearing a floatation vest, which serves to keep the body in an upright position and helps to prevent contact between the feet and the bottom of the pool [17]. The main advantages of the DWR-IT technique are buoyancy and lack of weight-bearing, minimizing the repeated stress and impact experienced in running on land, and low risk of musculoskeletal injuries. In addition, the individual can perform the same amount of work intermittently and with the same intensity as continuous exercise; however, the degree of fatigue after interval training is considerably smaller and more pleasant for this population [18].

However, little is known about the chronic effects of DWR-IT performed in a heated pool (32 °C), in the body composition evaluated by electrical bioimpedance and functional capacity measured by the six-minute walk test (6MWT) in overweight and middle-aged obese.

Given the above, the proposal of the present study for the advancement of scientific knowledge in the area of aquatic training and rehabilitation in overweight and obese women becomes relevant. Accordingly, the objective of the study will be to investigate the effect of the DWR-IT program on the body composition, functional capacity, and quality of life of overweight adults.

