### Exclusion criteria

The exclusion criteria included any history of neuromuscular and cardiorespiratory disease (self-declared) and any contraindications of aquatic physiotherapy: hydrophobia, cutaneous wounds, and infectious diseases [20]. Volunteers may not have participated in another physical training program for at least two months from the beginning of the data collection and may not participate in another training or nutritional monitoring program during the aquatic intervention. For those who use anti-hypertensive drugs and hormone replacement therapy, a change in medication class or dose will not be allowed. As a criterion of adherence after the training period, data from samples that did not obtain at least 80% frequency in the sessions will be excluded.

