## Discussion

The objective of the DWR-IT program will be to investigate the influence of the 12-week DWR-IT program on body composition, functional capacity, and quality of life of overweight adults. DWR-IT can be very beneficial to the health of overweight people since it increases energy expenditure besides promoting positive effects on aerobic capacity and cardiovascular function and improvement of perception of quality of life and sleep in overweight and obese subjects submitted to training [32, 34]. It is believed that in addition to having the aforementioned outcomes, the DWR-IT program may be beneficial to the health of overweight middle-aged adults since the physical properties and the heated temperature of the water promote pain relief, reduction of joint overload, and low risk of musculoskeletal injuries [35–37].

Pasetti; Gonçalves; Padovani [37] subjected 30 obese middle-aged women to 12 weeks of DWR (47 min per session, three times per week, and water temperature between 28 °C and 29 °C) in two different modalities: continuous training (*n* = 12, 45.3 ± 6.3 years) with an intensity of 70–85% of resting HR and interval training (TI; *n* = 18; 46.6 ± 7.9 years) with an intensity between 70% and 75% of HR of rest. Body composition was assessed by using adipometry, and the World Health Organization Quality of Life BREF (WHOQOL-BREF) was used for quality-of-life analysis. After the aquatic training period, there was a reduction in body density and percentage of fat and improvement in quality of life in both types of training [37].

However, in spite of the benefits promoted by DWR, no randomized clinical trials on DWR-IT were found in the literature in the past five years that investigated functional capacity, muscle strength, sleep quality, or quality of life analyzed by a specific instrument for this population. In addition, in the aforementioned clinical trials, adequate methodologies for the control of the intensity of the aquatic exercises were not used since the physiological adaptations were not considered during immersion in the cardiovascular system, particularly in the HR. Finally, food consumption (pre- and post-intervention) was not recorded, a fact that may interfere in the responses of the variables related to body composition [37–40].

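### The instruction to keep diet unchanged and the mid-study diet checks are described for the control arm only, so training and diet contributions to a body-fat difference may not be separable

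*Protocol article*

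**What the plan says.** The aim given in the Background is to "investigate the effect of the DWR-IT program on the body composition, functional capacity, and quality of life of overweight adults".

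The Control group section contains four provisions on diet and activity:
- an instruction: "Volunteers will be instructed not to change their daily usual activities or diet or participate in other physical activities";
- follow-up: "During intervention, the volunteers will be monitored by phone calls from the researchers every week";
- IPAQ and FFQ timing: "both will be applied before intervention, at week 6, and after the intervention period";
- a consequence: "If there are changes in dietary habits or level of physical activity, the volunteers will be excluded from the study".

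Randomization and allocation likewise attaches an instruction to the control group alone: its members "will be instructed not to engage in any kind of structured physical exercise training and to keep the life activities identified at baseline".

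The sections on the intervention period and the water group cover session frequency, group size, pool temperature, equipment, heart-rate targets, perceived effort and the weekly progression. They say nothing about diet.

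Three provisions are not limited to one arm. Under Exclusion criteria, volunteers "may not participate in another training or nutritional monitoring program during the aquatic intervention". The Abstract lists the FFQ in the general evaluation. Randomization and allocation applies the IPAQ before and after the intervention.

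The Discussion criticises earlier trials because "food consumption (pre- and post-intervention) was not recorded, a fact that may interfere in the responses of the variables related to body composition".

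**The concern.** The two arms are meant to differ in the training. As the text stands, they also differ in what they are told about eating and in how eating is followed during the 12 weeks. The ban on formal nutritional programmes does not cover a person who decides alone to eat less. That is a plausible step for overweight volunteers who have just started three supervised sessions a week, and it is a step that controls are told not to take.

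The protocol itself names food intake as something that can disturb body-composition results. At stake is the reading of a body-fat difference: how much comes from the training and how much from eating less alongside it. A weight-related part of the quality-of-life questionnaire could be touched in the same way.

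**Working it through.** **Text comparison**

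| Provision | Control group | Water group |
|---|---|---|
| Keep usual diet | Stated | Not stated |
| Weekly monitoring of diet and activity | Phone calls | Not stated (sessions monitor heart rate and effort) |
| FFQ and IPAQ at week 6 | Stated | Not stated |
| FFQ in the general evaluation | Yes (Abstract) | Yes (Abstract) |
| IPAQ before and after | Yes | Yes (Randomization and allocation, no arm restriction) |
| No formal training or nutritional programme | Yes (Exclusion criteria) | Yes (Exclusion criteria) |

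Randomization and allocation gives two IPAQ time points without naming an arm, while the Control group section gives three. Either week 6 is specific to controls, or the two sections disagree. The wording needs correcting in both cases.

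**Possible size**

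The protocol gives no figure for diet change, so there is no plan figure to reproduce. The only benchmark is the Abstract's expected fall in body fat of about 10%, read here as a relative change. Every other input below is an assumption.

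*Route 1: share of the arm that changes diet.* Contribution = (fraction of the water group that changes diet) × (extra fat loss from it, as % of baseline fat), with controls held at zero.

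| Fraction | 2% loss | 5% loss | 10% loss |
|---|---|---|---|
| 20% | 0.4 | 1.0 | 2.0 |
| 40% | 0.8 | 2.0 | 4.0 |
| 60% | 1.2 | 3.0 | 6.0 |

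In percentage points against the expected 10, this is 0.4/10 = 4% to 6.0/10 = 60% of the expected fall.

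*Route 2: energy deficit.* Assume 7,700 kcal per kg of fat and an 80 kg person with 38% fat.
- Baseline fat: 80 × 0.38 = 30.4 kg. A 10% fall is 3.04 kg.
- Duration: 12 × 7 = 84 days.
- Deficits of 100, 200 and 300 kcal/day: 8,400, 16,800 and 25,200 kcal.
- Divided by 7,700: 1.1, 2.2 and 3.3 kg, or 36%, 72% and 108% of 3.04 kg.

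These shares require the whole water group to average that deficit from the first day. If only 20% to 60% do so, the range is 0.20 × 1.09 = 0.22 kg (7%) to 0.60 × 3.27 = 1.96 kg (65%), close to route 1.

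**The case against.** The strongest reply has four parts.

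1. Randomisation still supports a comparison of assignment to the programme as delivered, with any diet change as part of it. This stands, so far as randomised participants stay in the analysis; the protocol's exclusion rules are a separate matter.

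2. Diet in the water group is not ignored. The FFQ is in the general evaluation, and the complaint about earlier trials was that intake went unrecorded before and after. This also stands: water-group intake can be described. Describing it does not hold it constant, and does not supply the missing instruction.

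3. The argument rests partly on silence in a condensed article. The schedule in Fig. 1 is not shown, and its legend names both arms and the FFQ. The Control group section also speaks generically of volunteers. Applying the week-6 questionnaires to both arms is therefore not excluded. That limits certainty about the schedule. The diet instruction, however, is stated, and it stands under one arm's heading; a schedule of assessments would not extend it to the other.

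4. The sample size rests on the six-minute walk test, not body fat, and the Abstract's aim names functional capacity first. This stands and limits the importance of the point.

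Unequal contact is in part inherent in a no-treatment control, and the weekly calls partly offset it. It is not counted here as a fault.

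A reader might infer that water-group members are free to diet, or that a body-fat difference cannot be attributed to the training at all. The documents support neither. The first reads a permission into missing text, and the second overlooks the first two replies.

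**Conclusion.** The point holds in a limited form. As written, the diet instruction, the weekly monitoring and the week-6 questionnaires are described for controls only, and the rule for all volunteers reaches only formal programmes. The effect of the programme as delivered can still be estimated. What may be lost is the separation of training and diet contributions to a body-fat difference. The asymmetry favours DWR-IT, because controls are told not to change their eating and the water group is not.

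The size is unknown. With 20% to 60% of the water group changing diet, the assumed inputs give roughly 4% to 65% of the expected 10% fall. A deficit averaged over the whole arm could reach all of it. These figures show that the bias could be material, not that it will be, since apart from the 12 weeks and the expected 10% no input comes from the protocol. The walk-test result is much less affected. This is a worthwhile, inexpensive improvement and does not undermine the trial's main comparison.

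**What to change.** - Move the instruction to keep the usual diet, and the FFQ and IPAQ at baseline, week 6 and end, to a section that applies to both arms. Align the IPAQ timing in Randomization and allocation with it.
- At one session each week, ask the water group the same diet and activity questions that controls are asked by phone.
- Report FFQ change by arm beside the body-composition result.
- Data collection is under way. For participants already enrolled without these provisions, word the body-composition conclusion as the effect of DWR-IT plus any accompanying diet change.

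The cost is protocol wording and one more FFQ/IPAQ round for about 15 people who already attend three times a week. The downside is slightly more questionnaire burden in the water group.

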#### Sample size

The sample size was performed on the basis of a pilot study, conducted previously with middle-aged women submitted to a DRW protocol [32]. Sample size calculation was performed by using G*Power version 3.1 software (Heinrich-Heine-Universität Düsseldorf, Düsseldorf, Germany). The maximum distance covered in 6MWT assessed before (566.2 ± 51.8 m) and after (625.1 ± 73.6 m) the DWR program was considered the main outcome. Significance level was set at 5% with 80% power. A sample of 12 participants per group was suggested. Given a possible 20% dropout rate, 15 participants will be required per group, thus totaling 30 participants.

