#### Analysis

The normality and homogeneity of data variance will be verified through the Shapiro–Wilk and Levene tests, respectively. For the variables with normal distribution, the two-way mixed-design analysis of variance (ANOVA) test (a repetition factor and a group factor), followed by Bonferroni post hoc, will be applied. For variables with non-normal distribution, the Wilcoxon tests will be used to compare the differences between times and the Mann–Whitney test to compare differences between groups. In this case, the Bonferroni adjustment will be used *a priori*. In all tests, the significance level of 5% will be considered. The effect size will be calculated by using Cohen’s d, and the results interpreted on the basis of Cohen as follows: small (0.21–0.49), medium (0.50–0.79), or large (≥0.80) [33].

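### The stated 80% power at 12 per group rests on within-group before/after values only and is not supported for the randomised between-group comparison

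*Protocol article*

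**What the plan says.** The Sample size section makes the six-minute walk test (6MWT) the sizing outcome: "6MWT assessed before (566.2 ± 51.8 m) and after (625.1 ± 73.6 m) the DWR program was considered the main outcome". These values come from a pilot "conducted previously with middle-aged women submitted to a DRW protocol". The error rates are "Significance level was set at 5% with 80% power", the result is "A sample of 12 participants per group was suggested", and attrition is added as "Given a possible 20% dropout rate, 15 participants will be required per group, thus totaling 30 participants". The software is named (G*Power 3.1). The test, the effect size entered and the pre-post correlation are not.

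The design is a parallel comparison. Participants are "randomly assigned by a computer-generated table of random numbers in a 1:1 proportion" (Randomization and allocation), and the Control group section says "The control group will not undergo any form of treatment". Under Analysis, normally distributed variables go to a "two-way mixed-design analysis of variance (ANOVA) test (a repetition factor and a group factor").

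**The concern.** The sizing inputs describe how one trained group changed over time. The trial asks whether the trained group changes more than an untreated group. The second contrast carries sampling error from both arms, so for the same 58.9 m and the same standard deviation (SD) of change it needs more people in each arm than the first needs in total. If the pilot's before/after contrast was sized and its n then used as n per arm, the stated power belongs to a different comparison.

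The stake is how a null result would be read. A non-significant 6MWT difference would be taken as coming from a trial with an 80% chance of detecting a 59 m benefit. If the correlation is about 0.5, the chance of missing that benefit is above one in three.

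**Working it through.** **Inputs from the protocol article (Sample size).** Before: mean 566.2, SD 51.8 m. After: mean 625.1, SD 73.6 m. Alpha 5%, taken as two-sided because sidedness is not stated. 12 per group, or 15 with 20% dropout.

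**Assumptions not in the document.** Pre-post correlation r, shown as a range. Control-group mean change of zero. 6MWT analysed at two times, before and after. All powers use the noncentral t distribution.

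**Step 1: reproduce the stated 12.**
- Difference = 625.1 − 566.2 = 58.9 m.
- SD of change = √(51.8² + 73.6² − 2r × 51.8 × 73.6). At r = 0.5 this is 65.5 m.
- dz = 58.9 / 65.5 = 0.90. A paired t-test then needs n = 12 (power 80.9%).
- A paired n of exactly 12 requires r of about 0.49 to 0.54. At r = 0.3 it would be 16, and at r = 0.7 it would be 9.
- Dropout: 12 / 0.8 = 15, which is correct.

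**Step 2: between-group power on week-12 values (no r needed).**
- SD = √((51.8² + 73.6²) / 2) = 63.6 m; d = 58.9 / 63.6 = 0.93.
- Power is 58% at 12 per group and 69% at 15. For 80%, 20 per group are needed.

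**Step 3: between-group power on change scores.** With two groups and two times, the group-by-time interaction of the mixed ANOVA equals a two-sample t-test on change. Two cases bracket the control arm:
- Case A: controls have the same SD of change as the trained arm.
- Case B: control SDs stay at 51.8 m at both times, so the control change SD is 51.8 × √(2(1 − r)). The SD used is the root mean square of the two arms' change SDs.

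| r (assumed) | 12 per group, A | 12 per group, B | 15 per group, A | 15 per group, B |
|---|---|---|---|---|
| 0.3 | 44% | 51% | 53% | 61% |
| 0.5 | 56% | 65% | 66% | 75% |
| 0.6 | 64% | 74% | 75% | 83% |
| 0.7 | 75% | 84% | 84% | 92% |

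A simulation at r = 0.5 with 12 per group gave 55.8% (A) and 64.9% (B). At that correlation 17 (B) to 21 (A) evaluable per group are needed for 80%. With 12 per group, 80% is reached at r of about 0.66 (B) or 0.75 (A).

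**Step 4: detectable difference at 80% power.** At 12 per group d = 1.20, so 1.20 × 63.6 ≈ 76 m. At 15 per group d = 1.06, so 1.06 × 63.6 ≈ 67 m. Both exceed the 58.9 m used for sizing.

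**The case against.** The strongest reply is that 12 does not identify the test. The paired calculation gives 12 only near r = 0.5. A between-group calculation on change, which is the planned interaction, also gives 12 per arm at r = 0.75 in case A, and 12 to 13 at about r = 0.66 in case B. A two-sample test using only the baseline SD of 51.8 m needs 14, with 76% power at 12. A condensed article may also leave the test and correlation to the full protocol. All of this stands. It is tempting to conclude that the authors used a paired calculation by mistake, or that true power is 56–65%. The document establishes neither: the first is an inference, and the second is the r = 0.5 slice of a range from 44% to 84% for r between 0.3 and 0.7.

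A reader might also infer that the pilot had no control arm. The section quotes only before and after values, and the pilot report is not available here, so that cannot be asserted. Nor can it be assumed that the 58.9 m contains a practice effect: the Six-minute walk test section plans two tests 30 minutes apart to deal with learning.

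Lastly, the abstract's Discussion expects a gain of about 25% in the 6MWT, roughly 142 m on 566.2 m, for which 12 per group would be ample. That is not the effect used for sizing, which is 58.9 / 566.2 = 10%.

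These points do not restore the 80%. The route through r of 0.66–0.75 needs a correlation and a control change that the section does not give. The baseline-SD route sets aside the larger follow-up SD printed beside it and still falls short. The point is not that detail is missing; a power figure is printed with its inputs, and those inputs contain no between-group effect.

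**Conclusion.** The point holds in this form: the printed inputs do not support 80% power at 12 per group for the randomised comparison. For a 58.9 m effect with no change in controls, power is 58% on week-12 values. On change scores it is 56–65% at an assumed r of 0.5, with 44–51% at r = 0.3 and 75–84% at r = 0.7. Only a correlation of about 0.66–0.75 or more would justify the claim, and none is stated. Full retention of 15 per group gives 69% on week-12 values and 66–75% on change scores at r = 0.5.

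The results rest on a two-sided 5% test, the pilot SDs carrying over to a trial that enrols both sexes, and zero control change. Any gain in controls would lower power further. The paired origin is a plausible explanation for 12, not an established one.

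**What to change.** Keep 30 participants and reword the Sample size paragraph:

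1. Check the G*Power record and state the test, effect size, sidedness and pre-post correlation that were entered. If it was a within-group calculation, say so.
2. Replace the 80% claim with the power for the between-group difference in 6MWT change at 12 and at 15 per group, over a stated range of correlations. The table above can serve for r = 0.3 to 0.7.
3. Give the between-group difference detectable with 80% power: about 76 m at 12 and 67 m at 15 per group, on an SD of 63.6 m.
4. State the assumed control-group change.

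The cost is one paragraph and a less favourable power statement. Recruitment does not change, which matters because Trial status reports that data collection is under way. The dropout step needs no correction.

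### Followed as written, the pre/post mixed ANOVA and the 80% attendance rule give a comparison of completers, which can be biased if loss depends on baseline or on response to training

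*Protocol article*

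**What the plan says.** The Sample size section makes the 6MWT the main outcome, using pilot values "assessed before (566.2 ± 51.8 m) and after (625.1 ± 73.6 m) the DWR program was considered the main outcome". It continues: "Significance level was set at 5% with 80% power", and "A sample of 12 participants per group was suggested". It then allows for losses: "Given a possible 20% dropout rate, 15 participants will be required per group, thus totaling 30 participants".

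The Analysis section names, for normally distributed variables, a "two-way mixed-design analysis of variance (ANOVA) test (a repetition factor and a group factor"), with Bonferroni post hoc tests. For other variables, "the Wilcoxon tests will be used to compare the differences between times and the Mann–Whitney test to compare differences between groups".

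The last sentence of Exclusion criteria removes, after training, the data of anyone who attended fewer than 80% of sessions. Randomization and allocation and Control group add exclusions for participants who depart from the instructions on activity or diet. The article names no rule that keeps a randomised participant in the efficacy analysis after leaving or after low attendance.

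**The concern.** Raising 12 to 15 per group protects the number of analysable participants. It does not protect the comparability of the arms, because a randomised comparison holds only for the people randomised. Two features of the plan remove some of them.

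- **The test.** With two occasions, a mixed ANOVA needs both values for each person. Someone with a baseline 6MWT but no final one contributes nothing, baseline included.
- **The attendance rule.** It deletes data that may well exist. Controls have no sessions, so it can act only on the water group.

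The demands on the arms also differ. The water group has 36 supervised sessions, while controls have weekly phone calls and questionnaires. Reasons for loss therefore need not match between arms. If they relate to baseline walking distance or to response, the estimated effect shifts. Body composition, strength, sleep and quality of life would go through the same analysis.

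**Working it through.** **Inputs from the Sample size section.** 6MWT before 566.2 m (SD 51.8) and after 625.1 m (SD 73.6), so the gain is 625.1 − 566.2 = 58.9 m. There are 12 analysable and 15 recruited per group, and the dropout allowance is 20%.

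**Assumptions not in the document.** Pre/post correlation r = 0.5 or 0.7; control SD 51.8 m at both times; control change 0; losses split equally between arms.

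**1. The plan's own figure.** 12 / (1 − 0.20) = 15 per group, 30 in total. This reproduces exactly and allows for 3 of 15 per arm, or 6 of 30.

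**2. What the test uses.** With two occasions, the group-by-time test equals a t-test on individual change, here in 12 + 12 complete pairs. SD of change in the water group is √(51.8² + 73.6² − 2r × 51.8 × 73.6) = 65.5 m (r = 0.5) or 52.6 m (r = 0.7). In controls it is 51.8 × √(2(1 − r)) = 51.8 or 40.1 m. The standard error is √((65.5² + 51.8²)/12) = 24 m, or √((52.6² + 40.1²)/12) = 19 m.

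**3. Attendance rule.** 0.80 × 36 = 28.8, so a water-group participant with 28 sessions or fewer is removed. No control can be.

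**4. Loss related to response, water group only.** If the 20% lost would have gained D metres less than those who stay, the completer estimate is too high by 0.2 × D: 4 m for D = 20, 8 m for D = 40, and 11.8 m for D = 58.9. Put another way, scoring three leavers as no change gives 58.9 × 12/15 = 47.1 m, a drop of 11.8 m. That is about half a standard error.

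Simulations with no true effect and 15 per arm:

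| Loss mechanism | Bias (m) | Type I error |
|---|---|---|
| Random, 20% per arm | about 0 | 4.8% |
| Water-group loss rises with poor change, odds ratio 1.6 per SD | +6.6 | 5.4% |
| Same, odds ratio 2.7 | +11.3 | 7.1% |
| Same, odds ratio 7.4 | +16.9 | 9.7% |
| Three lowest on change plus noise of equal variance, r = 0.5 / 0.7 | +15.5 / +12.7 | 10.6% / 11.3% |

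The odds-ratio rows use r = 0.5 and SD of change 65.5 m in both arms. The last row is strong selection: leavers gain about 76 m (r = 0.5) or 61 m (r = 0.7) less than finishers, more than the whole 58.9 m pilot gain.

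**5. Loss related to baseline, opposed in the two arms.** Suppose the three lowest baselines leave the water group and the three highest leave the controls. Dropping 3 of 15 at one end moves the remaining mean baseline by about 0.33 SD, or 0.33 × 51.8 ≈ 17 m. The slope of change on baseline is r × 73.6/51.8 − 1 in the water group (−0.29 or −0.01) and r − 1 in controls (−0.5 or −0.3).

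- r = 0.5: (−0.29 × 17) − (0.5 × 17) ≈ −13 m
- r = 0.7: (−0.01 × 17) − (0.3 × 17) ≈ −5 m

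Simulation agrees (−13.0 and −5.0 m, type I error 8.9% and 6.4%). Reversing the selection gives +13.5 and +5.6 m (9.2% and 5.7%).

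**6. What a likelihood model recovers.** Using every observed baseline, it brings the bias in step 5 to about 0. For the last row of the table it hardly helps: 13.9 / 12.1 m, against 14.9 / 12.1 m for completers in the same runs. With only two occasions, a leaver contributes a baseline value and nothing about response.

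**The case against.** The strongest reply is that this is silence. The article does not declare a completers set, inflating for dropout is routine, and missing-data handling may sit in an analysis plan that is not shown. Values could also be imputed before the named ANOVA. This stands in part: absence of a missing-data section would be no finding. What lifts the point above silence is that the article fixes a test that cannot use incomplete pairs and fixes a rule that deletes data from randomised participants. An analysis plan that kept everyone would have to depart from the attendance rule.

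Other limits also stand. Mann–Whitney does not by nature need both times; it does only if applied to change. Even so, someone with no final value cannot enter a comparison of final values.

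A reader might infer three stronger things that the document does not support:

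- **That the plan expects six people to leave.** It calls the 20% possible; it is an allowance, and the equal split is an assumption.
- **That the result is biased towards training with an inflated false-positive rate.** Nothing in the article shows that poor responders leave. Random loss gives no bias, baseline-related loss can go either way, and the mildest response-related case barely raises type I error.
- **That replacing the ANOVA with a mixed model cures the problem.** It removes at most about 1 m of the response-related bias.

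**Conclusion.** The point holds as a conditional risk built into the stated methods. Followed as written, the plan compares completers, and one of its two selection steps can act only on the water group.

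The size depends on why people are lost. It is none if loss is random. It is about 5 to 13 m in either direction if loss depends on baseline in opposite ways in the two arms. It is about 7 to 17 m towards training, with type I error about 5 to 11%, if poor responders leave the water group. Against the 58.9 m planning gain, that last range is 6.6/58.9 = 11% to 16.9/58.9 = 29%.

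These figures rest on 20% loss in each arm, the pilot SDs, and the assumed correlation and control values. The sample size arithmetic is not in dispute here. The change is worth making, because the trial is still in data collection and the remedy is cheap.

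**What to change.** 1. **Analysis:** state that all randomised participants are analysed as allocated, with all observed data, using a likelihood-based mixed model or multiple imputation that uses baseline. This corrects baseline-related loss only.
2. **Exclusion criteria:** move the 80% attendance rule to a secondary per-protocol analysis. Without this, final values collected from low attenders would still be deleted and step 3 could not work.
3. **Follow-up:** state that participants who stop training or fall below 80% attendance stay in the study and are invited to the already planned final assessment.
4. **Sensitivity analysis:** give missing final 6MWT values no change, or the mean control change, and report the result beside the main one. Steps 3 and 4 address response-related loss, which the model alone does not.

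The cost is new wording, a little more analysis and no new procedure. The downside is that the effect estimate will probably be smaller.
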